### Participants’ eligibility criteria

#### Sample size

Bird et al. [5] reported suitable comparative outcomes from a similar study. Following the stepped wedge study design with repeated cross-sectional samples recommendations of Barker et al. [16] and the applied parameters of Bird et al. [5], at least two clusters will be randomised at each step to ensure the nominal 5% significance level. Bird et al. [5] reached statistical significance using ANOVAs and *t* tests over three measures: ED presentations, hospital admissions and bed days. Pre verses post improvement for these three measures was 10%, 25% and 18% respectively. Following consultations with clinical and statistical experts, a conservative effect size across ED and in-patient services utilisation of 9%, a 10% intra-cluster correlation and between-cluster variations of 30% were assumed for the current study. The intervention will be staged in steps, each with at least two clusters/GPs, totalling a minimum of 10 GPs (clusters), who will each recruit 10–12 participants to the study. Allowing for 25% censoring, a sample size of 120 participants will be required, which will provide 80% power to detect a 9% difference (effect size) in service utilisation with statistical significance at the 5% level. The study design incorporates the effects of ‘time’. Sample size calculations were performed using the stepped wedge command in STATA 15 [18].

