### Statistical methods to assess intervention effect

The primary outcome measures, including Emergency Department (ED) presentations, hospital admissions, in-patient bed days, allied health and support services utilisation, will be analysed as panels between each cross-sectional time point of the stepped wedge design, comparing primary outcomes within and between clusters. Each cross-section will include participants undertaking the intervention as well as those receiving standard care (pre-intervention component). In addition to assessing intervention effects, the stepped wedge design can also model the effects of time to determine whether the time of intervention (intervening early versus intervening late) impacts the effectiveness of the intervention. Secondary outcome measures, including functional status, ISAR and QoL measures, will be compared for the pre versus post intervention periods, for each participant, and thus the participants will act as their own control. Participants’ experience of the OPEN ARCH intervention as measured by the Likert scale responses will be analysed using descriptive statistics.

Within-cluster and between-cluster variance, treatment outcomes for intervention versus pre-intervention, across time, will be examined by applying a generalised linear mixed model (GLMM), as recommended for small cluster designed stepped wedge studies [16]. GLMM models can be adjusted for unequal numbers within clusters and cope with non-parametric data distributions. Within the GLMM, primary and secondary outcomes will be assessed against time and intervention status, represented as fixed effects, while study clusters and clients will be represented in the model as random effects [16]. Secondary outcome analyses will include *t* tests (for continuous data), chi-square tests (for proportions) and GLMMs where applicable, to control for demographic differences. All statistical tests will be two-sided and performed using a 5% significance level with no adjustment for multiplicity. Data analysis will be performed using STATA version 15 [18].

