QALYs will be generated using a multi-attribute utility instrument, the EuroQoL 5-Dimension (EQ-5D-5L) scale [24]. This standardised, five-item descriptive system and visual analogue scale measures mobility, self-care, pain, usual activities and anxiety, and contributes to a ‘utility’ score. The AQOL-8D [32] instrument will be used to generate alternative QALYs. The AQOL-8D consists of eight dimensions: physical, including independent living, senses and pain; and psycho-social, including mental health, happiness, self-worth, coping and relationships. Utility weights for the AQOL were generated using the time-trade-off technique and Australian population sample. Due to its robust psychometric properties, the AQOL is recommended for use in epidemiologic studies where health-related QoL and utility data are required from older populations [33]. The AQOL has been used in Australian community older persons and Indigenous Australians studies [25].

The time horizon of the economic analysis will incorporate the lifetime of the cohort, through extrapolation of quality-adjusted survival from the end of the study period. A discount rate of 5% per year will be applied to both costs and outcomes [34]. The difference in costs and QALYs, between the intervention and pre-intervention periods, will be combined into the incremental cost-effectiveness ratio (ICER) with valuations of the willingness to pay for a marginal QALY to estimate the net monetary benefits for a decision to adopt the intervention:$$ \mathrm{ICER}=\frac{{\mathrm{Cost}}_{\mathrm{Int}}-{\mathrm{Cost}}_{\mathrm{Pre}-\operatorname{int}}}{{\mathrm{QALY}}_{\mathrm{Int}}-{\mathrm{QALY}}_{\mathrm{Pre}-\operatorname{int}}}, $$where Cost_Int_(Cost_Pre − int_) and QALY_Int_ (QALY_Pre − int_) are the mean cost and QALYs gained in the intervention (pre-intervention) periods, respectively. The maximum willingness to pay for a QALY will be assumed to be AUS$64,000 for the Australian setting [35]. The Markov state transition process will be applied to model participants’ probability of being readmitted to hospital, staying in the community or dying [36]. Sensitivity analysis will be performed to test variations in key parameters including the study perspective, the choice of the comparator and specific cost impacts.

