### Limitations

The study populations are, by definition, at risk of natural functional and cognitive decline that may be marked over the study period. Although the study design applies multiple methods to best capture intervention effects, the benefits in slowing down deterioration may not be successful in some participants due to their frailty. Within the quantitative methods are cross-sectional and case–control (pre–post intervention) analysis, which will assess between and within clusters differences. The pre–post analyses will utilise paired analyses where each participant acts as their own control. These methods plus the inclusion of qualitative surveys should tease out even minor benefits of OPEN ARCH, when presented with accelerated decline. The sample size calculation has allowed attrition, so these factors should allow statistical significant effect size within OPEN ARCH achievable.

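### Secondary outcomes are given both a paired pre/post comparison, which drops anyone without a post-step value, and a mixed model, with neither named as the main analysis

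*Protocol article*

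**What the plan says.** The section on statistical methods to assess the intervention effect states that functional status, ISAR and QoL "will be compared for the pre versus post intervention periods, for each participant, and thus the participants will act as their own control". The Limitations section repeats this: "The pre–post analyses will utilise paired analyses where each participant acts as their own control". It counts on these analyses, with the other methods, to bring out even small benefits, and takes reassurance from attrition having been built into the sample size.

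The same statistical section also places the secondary outcomes in a GLMM. Time and intervention status are the fixed effects, and cluster and participant are the random effects. It then lists t tests, chi-square tests and, where they apply, GLMMs for the secondary outcomes; the purpose it gives is control of demographic differences. No analysis is named as the main one. On error control: "All statistical tests will be two-sided and performed using a 5% significance level with no adjustment for multiplicity".

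Loss is expected. The Sample size section says: "Allowing for 25% censoring, a sample size of 120 participants will be required". The Participant recruitment section allows voluntary withdrawal, and withdraws all of a GP's participants if that GP moves practice or retires.

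**The concern.** A paired comparison needs a value on each side of the step. A participant lost before the first visit after the GP's step has only pre-step values and contributes nothing to it. The GLMM uses those values. The two analyses named for the same outcomes therefore rest on different sets of participants. With no main analysis fixed and no multiplicity adjustment, either could be put forward as the answer.

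The loss need not be random. The Limitations section itself expects that decline may be marked in this population. If people who decline faster are also more likely to leave before a post-step visit, the mean paired change describes a group that fared better than the one enrolled. Enlarging the sample for attrition protects precision; it does nothing about selective loss. At stake are research questions 2 (function and dependency) and 3 (quality of life). The primary service-utilisation outcomes are not affected by this point.

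**Working it through.** **Inputs from the document.** Total 120 and censoring 25% (Sample size); "totalling a minimum of 10 GPs (clusters), who will each recruit 10–12 participants to the study"; at least two GPs per step and equal length of intervention for every cluster (Randomisation of general practitioners); visits at −3, 0, 3, 6 and 9 months (Abstract). The number and dates of the steps are not in the text, and Fig. 2 is not shown. The cause and timing of the censoring are not stated.

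**The plan's own figure.** 90 / (1 − 0.25) = 120, so 120 is consistent with 90 retained (10 GPs × 9). The 90 is back-calculated. The 25% belongs to the service-utilisation calculation; applying it to the secondary outcomes is an assumption.

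**Share with no post-step value.** Let f be the month of the first post-step visit, T the length of follow-up and d = 0.25. The share lost before f is

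- linear: d × f / T
- constant rate: 1 − (1 − d)^(f/T)

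For three equal steps at 0, 3 and 6 months, f = 3, 6, 9 and T = 9:

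- linear: 8.3%, 16.7%, 25.0%; mean 16.7%, or 20.0 of 120
- constant rate: 1 − 0.75^(1/3) = 9.1%, 1 − 0.75^(2/3) = 17.5%, 25.0%; mean 17.2%, or 20.6 of 120

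Other calendars the text permits:

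| Assumed calendar | Linear | Constant rate | Of 120 |
|---|---|---|---|
| First post visit 3 months after each participant's own start | 8.3% | 9.1% | 10–11 |
| Steps at −3, 0, 3, 6 | 12.5% | 12.9% | 15–16 |
| Five steps, 15 months | 15.0% | 15.6% | 18–19 |
| Four steps, 12 months | 15.6% | 16.2% | about 19 |
| Steps at 0, 3, 6 | 16.7% | 17.2% | 20–21 |
| Steps at 3 and 6 only | 20.8% | 21.2% | 25–26 |

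With steps at 0, 3 and 6 but unequal numbers of GPs, the linear figure runs from (6 × 8.3 + 2 × 16.7 + 2 × 25.0)/10 = 13.3% to (2 × 8.3 + 2 × 16.7 + 6 × 25.0)/10 = 20.0%. The range is therefore about 8–21%. Loss bunched early would push it towards the ceiling of 25%. One departing GP removes 10–12 people, or 8.3–10% of 120.

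**Whether loss differs by step.** Under calendar steps it does (8.3% in the first step against 25.0% in the third, linear). If time runs from each cluster's own start, it is the same in every step.

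**Possible bias in the paired change (all inputs assumed).** 120 participants, steps at 0, 3 and 6, slopes with mean −0.5 and SD 1 per interval, measurement SD 0.7, and 25% lost by 9 months. About 120 × (1 − 0.172) = 99 pairs remain. If the odds of loss rise 1-, 1.5-, 2- or 3-fold per SD of faster decline, the paired change is too favourable by about 0, 0.5, 0.8 or 1.2 standard errors.

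**What the mixed model does (illustrative).** 120 participants, the same steps, a true effect of 0.30 SD, decline over time, and dropout depending on the last observed value. For convenience, cluster was fitted as a fixed effect. About 20% had no post-step value, yet all 120 entered the model, and its mean estimate was 0.29. The mean paired change was −0.04, but that gap includes the uncorrected time trend and cannot be put down to lost pairs alone.

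**The case against.** The strongest reply is that the remedy is already in the plan. The GLMM is named for secondary outcomes with suitable fixed and random effects, and it accepts participants who have only pre-step values. That stands. A reader might infer that people without a post-step value cannot be analysed at all, but this is true of the paired comparison only. It does not remove the point, because the paired comparison is what the plan states specifically for these outcomes, the Limitations section relies on it, and the GLMM is included only where applicable.

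A reader might also take about 17% as the plan's own loss figure. It is not: it needs three equal steps at 0, 3 and 6 months and 25% spread evenly over 9 months. That calendar also sits awkwardly with equal intervention time for all clusters, since it gives 9, 6 and 3 months of exposure by month 9.

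A reader might say that the results would describe survivors. The document does not equate censoring with death, gives no mortality rate, and describes withdrawal and GP departure as routes out. The accurate term is participants retained to a post-step visit.

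Finally, it is tempting to fault the plan for giving no value at death for function or quality of life. Such detail is commonly left to an analysis plan, which is not shown, and how to score death is a choice of estimand. The economic model does include "staying in the community or dying" among its states. No finding is made on this.

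**Conclusion.** The point holds in limited form. The plan assigns two analyses to the same secondary outcomes, does not rank them, and gives most prominence to the one that discards participants. If the 25% applies and loss is spread evenly, that analysis drops roughly 8–21% of participants. Heavier loss from later steps follows only if steps fall on calendar dates. A favourable bias follows only if those lost decline faster than those retained. The document makes this plausible but does not show it; if loss is unrelated to decline, this bias is nil. The figures in standard errors are illustrations under assumed odds ratios, not estimates for this trial.

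**What to change.** In the statistical methods section and in Limitations, name the GLMM already described (time and intervention status fixed; cluster and participant random) as the main analysis of the FIM, ISAR, EQ-5D-5L and AQOL-8D. State that it is fitted to all 3-monthly values of every enrolled participant, including those with only pre-step values, and label the paired tests descriptive. In Limitations, do not offer the attrition allowance as protection against selective loss. Add that the model is valid when loss depends on observed values but does not resolve deaths or loss that depends on unobserved values, and carry that caveat into the conclusions on research questions 2 and 3.

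The cost is wording in two sections. No new data are needed and the model is already planned.

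### Secondary outcomes get both a paired pre-post test without time adjustment and a time-adjusted mixed model; nothing says which decides, and expected decline biases the first

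*Protocol article*

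**What the plan says.** All of the analysis text is in the protocol article, section *Statistical methods to assess intervention effect*.

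- **Paired comparison.** Functional status, ISAR and quality of life "will be compared for the pre versus post intervention periods, for each participant, and thus the participants will act as their own control". The *Limitations* section confirms the pairing: "The pre–post analyses will utilise paired analyses where each participant acts as their own control".
- **Time-adjusted model.** Within the GLMM, "primary and secondary outcomes will be assessed against time and intervention status, represented as fixed effects", with clusters and clients as random effects.
- **List of tests.** The next sentence reads: "Secondary outcome analyses will include *t* tests (for continuous data), chi-square tests (for proportions) and GLMMs where applicable, to control for demographic differences".
- **Error rate.** "All statistical tests will be two-sided and performed using a 5% significance level with no adjustment for multiplicity".

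The *Limitations* section describes the study population as "at risk of natural functional and cognitive decline that may be marked over the study period". It then says that the methods, together with surveys, "should tease out even minor benefits of OPEN ARCH, when presented with accelerated decline".

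**The concern.** The same outcomes have two analyses of different validity. Every cluster crosses from standard care to the intervention and none crosses back, so each participant's post period is later than the pre period. A within-person contrast cannot separate the effect of the intervention from whatever happens with time. In this population the protocol expects that to be decline.

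The GLMM with time as a fixed effect deals with the problem. But the sentence that follows it restricts GLMMs for secondary outcomes to cases where they apply, and gives their purpose as control for demographic differences, with no mention of time. No rule says which result is the conclusion, and each test is made at 5%. The article could therefore support two different answers to the research questions on functional decline and on quality of life.

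**Working it through.** The plan gives no figure to reproduce here. The check has three steps.

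**1. What the paired contrast estimates.** Let the trend be g per month (negative for decline) and the intervention effect be b. A participant's mean post value minus mean pre value has expectation b + g × (mean post time − mean pre time). Collection times are −3, 0, 3, 6 and 9 months (*Abstract*, methods). If all periods on either side of the crossing are averaged:

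| Crossing after month | Mean pre time | Mean post time | Gap (months) |
|---|---|---|---|
| −3 | −3 | 4.5 | 7.5 |
| 0 | −1.5 | 6 | 7.5 |
| 3 | 0 | 7.5 | 7.5 |
| 6 | 1.5 | 9 | 7.5 |

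On the four points 0 to 9 the gap is 6 months at each crossing. The trend does not average out across clusters. With the 7.5-month gap, the bias is 7.5/3 = 2.5 times the change per three-month period.

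**2. How often the paired test rejects when b = 0.** The sample size section gives 120 participants and 25% censoring, so I take 120 × 0.75 = 90 evaluable. Let d be the decline over the gap divided by the SD of the paired change. The values of d are assumed. The two-sided rejection probability is Φ(d√90 − 1.96) + Φ(−d√90 − 1.96), with √90 = 9.487.

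| d | d√90 | Rejection probability |
|---|---|---|
| 0 | 0 | 0.050 |
| 0.1 | 0.949 | 0.158 |
| 0.2 | 1.897 | 0.475 |
| 0.3 | 2.846 | 0.812 |

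Over a 7.5-month gap these values of d are 0.04, 0.08 and 0.12 SD of the paired change per three months (each divided by 2.5). With a t distribution in place of the normal, the last three probabilities are 0.155, 0.467 and 0.804. If all 120 participants are evaluable, they are 0.192, 0.584 and 0.903.

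**3. The two planned analyses side by side.** A simulation of 1,000 runs per scenario used 10 clusters, 9 evaluable participants each, 5 periods and 4 steps. The ICC was 0.10, the protocol's value for service utilisation. The within-person correlation was assumed to be 0.7. The mixed model had period and intervention as fixed effects and cluster and participant as random effects, with variances treated as known. Here the unit is the SD of the outcome, not of the paired change.

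| Decline per 3 months | True benefit | Paired t: estimate, rejects | Mixed model: estimate, rejects |
|---|---|---|---|
| 0 | 0 | 0.00, 5% | 0.00, 4% |
| 0.05 SD | 0 | −0.13, 58% | 0.00, 4% |
| 0.10 SD | 0 | −0.25, 99% | 0.00, 6% |
| 0.10 SD | 0.25 SD | 0.00, 5% | 0.25, 76% |

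The paired estimates agree with step 1: 2.5 × 0.05 = 0.125 and 2.5 × 0.10 = 0.25. In the last row the decline cancels the benefit exactly.

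**The case against.** The strongest reply is that the article already plans a time-adjusted analysis for these outcomes. It also says that secondary analyses will include several methods, which can be read as a complementary list whose ranking is left to an analysis plan that is not shown. The first part stands. A reader might infer that the research questions on function and quality of life rest only on an uncontrolled before-after comparison, and the GLMM sentence rules that out. The second part stands only in part. An unstated ranking alone would be no finding, but the article states a biased test of effect and confines the valid model to a purpose other than time.

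Other stronger readings are tempting but not supported:

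- **Clustering.** One might infer that ignoring GP clusters invalidates the paired t test. A stable GP effect cancels in a within-person difference, and the simulation gave 5% rejection with no decline and no effect. Only GP effects that vary over time would matter, and the article gives no information on those.
- **Chi-square.** One might infer that the same people are treated as independent samples. The article does not specify the form of the test, and *Limitations* says the pre-post analyses are paired.
- **False benefit.** One might infer that regression to the mean could create an apparent gain. The eligibility criteria rest on age and complex needs, not on an extreme outcome score. The mechanism that the article documents, decline, works against the intervention.
- ***Limitations*.** The claim about minor benefits is made for the methods together, including the cross-sectional analysis and surveys. It is wrong for the pre-post part, not necessarily for the whole.

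**Conclusion.** The point holds in this limited form. The article gives two analyses of unequal validity for functional status, ISAR and quality of life. The paired one is wrong as a test of effect, because it estimates effect plus time trend. If decline occurs, the paired test can miss a real benefit or show apparent harm. The optimism in *Limitations* about detecting minor benefits under accelerated decline does not hold for the pre-post analyses.

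The direction follows from the design and the protocol's own expectation of decline. The size does not. Rejection rates of about 16%, 48% and 81% rest on assumed declines, an inferred 90 evaluable participants, and a complete wedge with all periods averaged. The design figure is not shown, and the statement that all clusters receive the intervention for the same length of time may imply another layout. These rates describe the paired test alone, not the full set of planned analyses. The outcomes are secondary and the primary analysis is untouched, so the severity is below must-fix.

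**What to change.** In *Statistical methods to assess intervention effect*:

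- Name the GLMM already described (time and intervention status as fixed effects, cluster and client as random effects) as the deciding analysis for FIM, ISAR, EQ-5D-5L and AQOL-8D.
- Delete the phrase that limits secondary GLMMs to where they apply and to demographic differences. Demographic covariates can still be added to the model.
- Keep pre and post summaries, but as description only. Do not use t or chi-square comparisons as tests of effect.

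In *Limitations*, state that the paired pre-post comparisons do not separate benefit from decline, and that the time-adjusted model is relied on for that.

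The change is to wording only. It needs no new data and no design change. The cost is wider intervals than the paired test would give.

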This trial aims to address the gap by delivering and evaluating a comprehensive, multidimensional geriatric assessment with care coordination in a community setting. The Older Persons ENablement And Rehabilitation for Complex Health conditions (OPEN ARCH) model of care evolved from an initial study that explored patient well-being post hospitalisation [10]. That completed study examined patients’ transition back to primary healthcare and their access to allied health and social support services within the community [10]. This current OPEN ARCH intervention builds on previous research [4, 10] and extends the service to preventative service delivered in a community setting; it creates a direct path from a general practitioner (GP) to a community-based geriatrician-led Healthy Ageing Clinic for comprehensive interdisciplinary assessment and care planning. The OPEN ARCH intervention will facilitate timely access to primary healthcare, including allied health services and social supports within the community. It is envisaged that the OPEN ARCH intervention will delay health decline by increasing individual capacity, when supported by a team of community healthcare professionals, who monitor and manage the community-dwelling complex older patients within the community. Such coordinated care support is expected to reduce the likelihood of the aforementioned cascade of events that leads to hospitalisation, and eventual loss of independence following hospital discharge.

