### Randomisation of general practitioners

All recruited GPs will be randomised as ‘clusters’ at baseline using simple randomisation [17]. Such cluster randomisation allows control for the ‘between GPs variance’. A minimum of two clusters (two GPs) will be commencing the intervention at each step, as per the recommendations of Barker et al. [16], to ensure that the intervention effect estimator maintains the nominal 5% significance level and is reasonably unbiased. All clusters will ultimately receive the intervention for the same length of time.

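### The on/off GLMM understates a benefit that is delayed or builds up, and its time and intervention main effects cannot answer the protocol's early-versus-late question

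*Protocol article*

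**What the plan says.** The section on statistical methods in the protocol article compares intervention with pre-intervention periods in a GLMM. On the fixed part it says that "primary and secondary outcomes will be assessed against time and intervention status, represented as fixed effects". On the random part, "study clusters and clients will be represented in the model as random effects". It names no term for time since a GP's start and no interaction of time with intervention.

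The same section says that modelling the effects of time allows the design "to determine whether the time of intervention (intervening early versus intervening late) impacts the effectiveness of the intervention".

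Two other statements bear on the point. The Background expects that "the OPEN ARCH intervention will delay health decline by increasing individual capacity", with a community team monitoring and managing patients. The section on randomisation of GPs says: "All clusters will ultimately receive the intervention for the same length of time".

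**The concern.** A single on/off term assumes that the whole effect is present from the first treated window and then stays the same. The intervention is a sequence (geriatric assessment, case conference, care plan, linkage to services) with a preventive aim, so an effect that takes a quarter to appear, or grows, is plausible. In a stepped wedge with a categorical time effect, the on/off estimate is then not an average over exposure. Windows of longer-treated GPs serve partly as comparators for newly treated GPs, so later benefit can count against the intervention. A null result could be read as no effect when the intervention works.

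The early-versus-late aim is a second, separate matter. It asks whether the intervention effect changes with timing, while the stated model allows only one effect.

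**Working it through.** **Early versus late (no layout needed).** Write the stated model as g(E[Y]) = β_t + θ·X_it + GP intercept + client intercept, with X_it = 1 once GP i has started. The effect is θ for every start step and every calendar time. Effect in early starters minus effect in late starters is θ − θ = 0 by construction. The β_t describe secular trend only.

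**Delayed benefit.** The plan states no figure on this point, so there is none to reproduce.

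Inputs from the article:
- Time points at −3, 0, 3, 6 and 9 months, giving four three-month windows (Abstract).
- At least 10 GPs with 10–12 participants each, 25% censoring, ICC 10% and a 9% effect (Sample size).
- At least two GPs per step (Randomisation of GPs).

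Assumed, because the schematic is not shown:
- The step layout.
- 9 or 12 patients per GP.
- Within-patient correlation 0 to 0.7.
- Total variance 1.

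Method: let X hold period indicators and the on/off column, Z the indicators of exposure quarter 1, 2, 3, and δ the true effects by quarter. The GLS on/off estimate has expectation Σ w_e·δ_e, where w is the on/off row of (X′V⁻¹X)⁻¹X′V⁻¹Z. The weights sum to 1, so a constant effect is recovered exactly.

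Worked case: three steps of 3/3/4 GPs (9, 6 and 3 months of exposure in the data), 9 patients, no within-patient correlation. The weights are 1.058, 0.154 and −0.212.
- Reduction 0/9/9%, true mean 6%: 9 × (0.154 − 0.212) = −0.5%.
- Reduction 3/6/9%, true mean 6%: 3 × 1.058 + 6 × 0.154 − 9 × 0.212 = 2.2%.

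Ranges over the assumptions, with positive meaning benefit:

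| Four-window layout | 0/9/9 (true mean 6%) | 3/6/9 (true mean 6%) |
|---|---|---|
| Two steps | −2.9 to −2.3% | 1.1 to 1.5% |
| Three steps | −1.5 to −0.5% | 1.6 to 2.2% |
| Four steps, last not yet treated | 0.9 to 1.9% | 3.0 to 3.6% |

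**Equal exposure.** Five steps, three treated windows per GP, 10 patients, GP intercept only, ICC 0.10:
- One pre-window: weights 0.883, 0.295, −0.178. The 0/9/9 curve gives 9 × 0.117 = 1.1%, and 3/6/9 gives 2.8%.
- Common calendar start: weights 0.763, 0.314, −0.077. The 0/9/9 curve gives 9 × 0.237 = 2.1%, and 3/6/9 gives 3.5%.
- Adding a within-patient correlation of 0.7 lowers 0/9/9 to about 1.5% with a common start. With one pre-window the weights become about 1.20, 0.28, −0.48, and 0/9/9 gives 9 × (0.28 − 0.48) = −1.8%.

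**Longer layouts and link function.** With four steps over five windows, or five steps over six, a linear build-up is estimated at 29% and 25% of its average. With a Poisson log link on expected counts in these two layouts:
- No effect for six months, then an 18% reduction, gives an on/off rate ratio of 1.06 and 1.05.
- An 18% reduction after one quarter (average ratio 0.86 and 0.85) gives 1.00 and 0.97.

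**Precision of the alternative.** A model with exposure-quarter indicators was full rank in every layout tried. The standard error of its averaged effect, relative to the on/off term, is the square root of the variance ratio: √1.27 = 1.13 (equal exposure, common start), √2.11 = 1.45 (four steps, five windows) and √2.22 = 1.49 (five steps, six windows). In the four-window layouts it is about 1.2–1.5 with three or four steps and 1.7–2.0 with two.

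**The case against.** A GLMM with time and intervention status is a standard stepped wedge analysis, and the article does not say that interactions are excluded. A condensed article may leave such terms to an SAP. This has force against calling the bare model an error, and it is why the on/off model should stay. It does not remove the mismatch: the article states the fixed effects and, in the same section, an aim that they cannot serve.

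The Background supports a preventive effect but gives no lag or build-up. Part of the primary outcome, allied health and support service use, could change promptly after referral. So delay is an assumption, and the bias is conditional on it. That stands.

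A reader might infer that the planned analysis will turn benefit into apparent harm. The documents do not support this. The layout is unknown, and with a one-quarter lag the sign reverses in the assumed two- and three-step layouts but not in the four-step one. Under equal exposure it stays positive with a GP intercept alone. The 3/6/9 curve did not reverse in any of the four-window or equal-exposure layouts. A low ICC also softens the problem: at 0.01, five-step equal exposure with a GP intercept alone gives about 4.0% for 0/9/9.

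A reader might also infer that a time-since-start model settles early versus late. It does not. It assumes the same effect at a given exposure quarter for early and late starters.

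**Conclusion.** The point holds in two parts. First, with no assumption about layout, main effects of time and intervention cannot show whether early or late intervention changes effectiveness. Second, if benefit is delayed or builds up, the on/off coefficient understates the average effect. A true mean of 6% is estimated at about 3.6% or less in the four-window layouts, and it is attenuated under equal exposure at ICC 0.10 as well. Sign reversal depends on the layout, the correlations and the length of the lag, and should not be claimed as the expected result. An immediate, constant effect carries no bias. The sizes rest on the assumed layouts, patients per GP and within-patient correlations. Adding supporting analyses is worthwhile; replacing the planned model is not called for.

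**What to change.** Keep the on/off GLMM as planned and pre-specify two supporting analyses.

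(a) Refit the same GLMM with intervention status replaced by quarters since that GP's start. Report the effect averaged over exposure quarters with its interval. State that a null on/off result will not be read as no effect if the two fits disagree.

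(b) For the early-versus-late statement, add an intervention-by-start-step or intervention-by-calendar-time term, since fit (a) alone does not answer that question.

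The cost is two model fits and a sentence of interpretation. The exposure-averaged effect is less precise: its standard error is about 1.1–1.6 times that of the on/off term in most layouts with three or more steps, and up to about 2 times with two steps or in the least favourable other layouts. With about 10 GPs the interaction in (b) will be imprecise. Both should therefore be labelled as supporting.
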